## Abstract

**Background:**

Pain is a complex polygenic trait whose common genetic underpinnings are relatively ill-defined due in part to challenges in measuring pain as a phenotype. Pain sensitivity can be quantified, but this is difficult to perform at the scale required for genome wide association studies (GWAS). Existing GWAS of pain have identified surprisingly few loci involved in nociceptor function which contrasts strongly with rare monogenic pain states. This suggests a lack of resolution with current techniques. We propose an adaptive methodology within a recall-by-genotype (RbG) framework using detailed phenotyping to screen minor alleles in a candidate ‘nociceptor’ gene in an attempt to estimate their genetic contribution to pain.

**Methods/design:**

Participants of the Avon Longitudinal Study of Parents and Children will be recalled on the basis of genotype at five common non-synonomous SNPs in the ‘nociceptor’ gene transient receptor potential ankylin 1 (*TRPA1*). Those homozygous for the common alleles at each of the five SNPs will represent a control group. Individuals homozygous for the minor alleles will then be recruited in a series of three sequential test groups. The outcome of a pre-planned early assessment (interim) of the current test group will determine whether to continue recruitment or switch to the next test group. Pain sensitivity will be assessed using quantitative sensory testing (QST) before and after topical application of 10% cinnamaldehyde (a TRPA1 agonist).

**Discussion:**

The design of this adaptive RbG study offers efficiency in the assessment of associations between genetic variation at *TRPA1* and detailed pain phenotypes. The possibility to change the test group in response to preliminary data increases the likelihood to observe smaller effect sizes relative to a conventional multi-armed design, as well as reducing futile testing of participants where an effect is unlikely to be observed. This specific adaptive RbG design aims to uncover the influence of common *TRPA1* variants on pain sensation but can be applied to any hypothesis-led genotype study where costly and time intensive investigation is required and / or where there is large uncertainty around the expected effect size.

*Trial registration*: ISRCTN, ISRCTN16294731. Retrospectively registered 25th November 2021.

**Supplementary Information:**

The online version contains supplementary material available at 10.1186/s12920-022-01156-5.

## Background

Pain is a cognitive motivational state whose function is to minimise the risk of injury and to aid healing and recovery. There is a large variation across the population in pain experience as well as apparent susceptibility and twin studies have suggested that the genetic heritability may be moderate (35–50%) [1]. There are a number of examples of rare, highly penetrant single nucleotide polymorphism (SNPs) modulating pain sensitivity, including in transient receptor potential ankyrin 1 (*TRPA1*) [2, 3]. However, the genetic contribution to most acute and persistent pain is likely comprised of the cumulative effect of many SNPs with small effects [4].

The most common approach to understanding the association of individual SNPs in polygenic traits is to perform a genome wide association study (GWAS). However GWAS have more power if there is a well-defined, relatively homogeneous phenotype with which to search for genetic associations across individuals. The more heterogeneous the phenotype, the lower the probability of identifying meaningful associations. Pain is a complex biological, psychological and social phenomenon [5] where multiple pain mechanisms can be in play to differing extents at any one time. This results in an intrinsically heterogeneous phenotype even within clinically defined patient populations. This heterogeneity within pain phenotypes then requires a very large cohort for SNP effects to be observed in a GWAS which, due to practicality, limits the assessment of individuals to phenotyping tools that are often questionnaire-based, reliant on recall and therefore lack mechanistic specificity and are subject to report bias. A recent large-scale GWAS of multisite chronic pain conducted in the UK Biobank identified 76 independent genome-wide significant SNPs and estimated SNP heritability to be 10% [6]. This GWAS revealed similarities in the genetic profile of pain to common comorbid mental health conditions like major depressive disorder and generalised anxiety disorder. However, none of the associated SNPs were specific to the pain transduction pathway (including *TRPA1*) likely due to a lack of mechanistic sensitivity of the questionnaire approach.

Quantitative sensory testing (QST) uses controlled and reproducible stimuli to evoke a percept, which is measured using standardized language and pain scales. This approach enables quantification of an individual’s pain perception with more mechanistic precision than simple pain scores. The German Research Network on Neuropathic Pain (DFNS) have produced a comprehensive protocol and corresponding reference values which is an accepted standard in the field [7]. This protocol has been used to identify defined patient sub-populations and predict efficacy of drugs [8, 9]. Unfortunately, the cost and time required to test the number of participants required to perform a GWAS of pain sensitivity using QST makes such an approach challenging, although a study design has recently been proposed to test 1500–2000 healthy young subjects [10].

Where there is a strong hypothesis for a candidate gene to alter function, informed by knowledge of biological mechanisms, a recall-by-genotype (RbG) study can be used. In this design, individuals with known variations in candidate genes are recalled for targeted detailed phenotyping. This selective recruitment reduces genetic variability of the cohort within genes expected to be involved in the trait of interest and allows more robust phenotyping with lower measurement error, therefore increasing the power of the study to detect a difference (as compared to random sampling from the population), allowing the study to be conducted on a smaller cohort than would otherwise be required. Given random allocation of alleles at conception, the RbG design generates study groups in which confounding factors are on average equal enabling a potentially informative assessment of genotypic association [11]. There is a wealth of evidence from studies of fundamental pain neurobiology that can be used to inform mechanistic candidate gene investigations [12], such as the gene families of transducer proteins involved in sensing threatening stimuli.

*Indicates the reference allele in dbSNP – note that this is different to the predicted ancestral allele for rs7819749. SNP information is extracted from dbSNP and is therefore reported in the forward orientation whilst *TRPA1* itself maps to the reverse strand. dbSNP: build 154, GRCh38, last accessed: 27th January 2021) [17]. SNPs in high linkage disequilibrium as reported in LDLink using GBR cohort [23]: Group 2 LD: r^2^ = 0.51. Group 3 LD: r^2^ = 1. AITC: Allyl isothiocyanate, ALSPAC: Avon Longitudinal Study of Parents and Children, CFA: Coal fly Ash, DTBP: 3,5-*Ditert*-butylphenol, MAF: minor allele frequency, SNP: single nucleotide polymorphism

^#^Deering Rice et al., 2015 expressed TRPA1 with site directed mutations HEK cells; “response” relates to calcium flux evoked by the stated TRPA1 agonists

^a^In all cases the major allele is also the designated ancestral allele in dbSNP

^b^MAF is as reported in dbSNP

^c^MAF in 1000 Genomes Project phase3 release V3+

Adaptive study designs are commonly used in clinical trials to optimise the number of participants recruited to trial arms (for a review see [24]). Adaptive trial designs are commended within the Initiative on Methods, Measurement, and Pain Assessment in Clinical Trials (IMMPACT) guidelines [25]. A typical adaptive design utilises interim analysis performed by an independent data monitoring committee after a pre-specified number of individuals are recruited. The committee can be unblinded to the treatment group allocation to enable evaluation of the probability of success—either futility or efficacy, balanced against any associated toxicity findings. At interim assessment, the committee can choose to adapt the study which can mean: study termination, sample size adjustments, altered recruitment strategy or even change to the primary endpoints (for a review see Pallmann, Bedding [26], Bauer and Brannath [27]).

When applied in the context of a RbG study, an adaptive design should increase the likelihood of observing smaller SNP effects on phenotype, prevent unnecessary testing in the case of futility and enable screening of multiple alleles by altering the recruitment strategy early if futility is demonstrated. Due to its prevalence in clinical drug trials the statistical implications of interim assessment have been well studied [28]. To the best of our knowledge, the proposed adaptive RbG study design is a novel methodology that offers a number of advantages and is potentially generalisable to many other settings and study questions.

## Methods/design

This study aims to investigate the association of common variants of *TRPA1* with altered pain sensitivity within the Avon Longitudinal Study of Parents and Children (ALSPAC) cohort who are a regionally representative cross-sectional population aged around 30 years (with a correspondingly relatively low incidence of chronic pain). Five *TRPA1* SNPs known to introduce missense mutations and with minor allele frequencies of > 1% hypothesized to impact TRPA1 function (see Table 1) will be investigated. The effect of these five SNPs will be assessed in three groups due to the high linkage disequilibrium between two pairs of minor alleles. QST results from the individuals in these three test groups will be compared to those of a reference group who are homozygous for the major (ancestral) allele at all five SNPs. The results will be subject to planned interim assessments for futility to alter recruitment if there is low probability of success of detecting a phenotype for a given allele until a maximum of 100 participants have been assessed.

Heat pain threshold is the primary outcome in this study as in both healthy volunteers and animal models TRPA1 is involved in determining heat pain sensitivity, particularly in the sensitised state [29–32].

### Ethical considerations and informed consent

The study was presented to the ALSPAC Original Cohort Advisory Panel (OCAP). Ethical approval for the original study was obtained from the ALSPAC Ethics and Law Committee and the Local Research Ethics Committees. Informed consent for the use of data collected via questionnaires and clinics was obtained from participants following the recommendations of the ALSPAC Ethics and Law Committee at the time. The proposal number was B3236 and the approval number is 94082. All subjects will provide written informed consent and will be reimbursed for their time and travel costs. This study is sponsored by the University of Bristol.

### Participant recruitment

ALSPAC is a transgenerational prospective birth cohort that began with the recruitment of 14,541 pregnant women resident in Avon, UK with expected dates of delivery 1st April 1991 to 31st December 1992. Since then, the health and development of mothers and their children has been followed across the life-course. When the oldest children were approximately 7 years of age, an attempt was made to bolster the initial sample with eligible cases who had failed to join the study originally. As a result, the total sample size for analyses using any data collected after the age of seven is therefore 15,454 pregnancies, resulting in 15,589 foetuses. Of these 14,901 were alive at 1 year of age [18, 33, 34]. Please note that the study website contains details of all the data that is available through a fully searchable data dictionary and variable search tool: http://www.bristol.ac.uk/alspac/researchers/our-data/.

For this study, members of the original ALSPAC cohort (individuals born between 1990 and 1992) will be selected for an invite based on their genotype at the five SNPs using previously acquired genetic data, please see Additional file 1, ALSPAC: Genotyping and imputation description. Individuals with the required genotypes will be identified using genome-wide data, as imputed to the Haplotype Reference Consortium (v1.1) reference panel [35]. Only individuals whose genotypes at the five SNPs were imputed with a probability of > 0.99 were eligible for invite. The SNPs of interest were rs7819749, rs959976 with rs920829, rs16937976 with rs13268757 (dbSNP build 154, GRCh38.p12 [17]) and a control group of individuals homozygous for all five major alleles (see Table 1 for details). Investigators and participants will remain blind to genotype throughout the recruitment and data collection phases of the study.

Invitations will be sent to selected ALSPAC participants, together with a participant information sheet and reply slip. All participants who volunteer to take part will undergo telephone screening with exclusions applied based on the following criteria:Neurological disorders including peripheral neuropathyRegular use of analgesicsAny pain medication taken within 24 h of QSTPregnancyAcute or chronic pain conditionsSevere anxiety/depressionAllergy to cinnamon, mustard, alcohol/chlorhexidine wipes, latex.Use of non-prescribed or recreational drugs (assessed by questionnaire).

## Data collection

### Quantitative sensory testing

The participants will be assessed using quantitative sensory testing (QST, see protocol in Fig. 1) before and after sensitisation by topical application of 10% cinnamaldehyde (a known activator of TRPA1). QST paradigms are based upon the DFNS protocol [7], streamlined in line with the primary hypothesis to omit some non-nociceptive assessments.

**Fig. 1 Fig1:**
[figure not shown]
Schematic of Quantitative Sensory Testing (QST) protocol. Top row represents the baseline QST including thermal and mechanical stimulation. The middle row shows capture of baseline cutaneous perfusion using the FLPI in the 4 × 4 cm region of interest, application of 10% cinnamaldehyde and then capture of the post challenge cutaneous perfusion. The bottom row represents the post challenge QST. (Figure adapted from Rolke et al. [7]). CDT, cold detection threshold; WDT, warm detection threshold; CPT, cold pain threshold; HPT; heat pain threshold; MDT, mechanical detection threshold; MPT, mechanical pain threshold; MPS; mechanical pain sensitivity; Brush, presence or absence of brush allodynia; Pressure, deep pressure pain threshold; FLPI, full field laser perfusion imaging; Cinn, cinnamaldehyde

Thresholds for heat and cold detection and pain will be tested using a thermode (Medoc TSA-II, Medoc, Israel, or similar) on the right volar forearm. The temperature of the thermode will change at 1 °C per second until the participant reports either detection of temperature change (cool and warm detection threshold), or detection of pain (heat or cold pain threshold) via a mouse click. The thermode then returns to a neutral temperature of 32 °C. The first trial will be discarded as an acclimatisation and then followed by 3 experimental repeats.

Thresholds for innocuous mechanical stimuli will be assessed using calibrated von Frey filaments (TouchTest; Stoelting, USA) via the method of levels. Mechanical pain thresholds, again via the method of limits, and stimulus response curves will be assessed using calibrated punctate needle stimulators (PinPricks; MRC Systems, Germany). For the stimulus response curve participant numerical pain ratings from 0 (no pain) to 100 (worst imaginable pain), will be assessed 5 times with 7 filaments exerting forces from 8 to 512 mN presented in a randomised manner. Dynamic mechanical allodynia will be assessed with 5 standardised brush strokes (SenseLab; via MRC Systems, Germany). Pressure pain sensitivity will be assessed with an algometer (Somedic, Sweden) applied over the muscles of the right volar forearm. Skin perfusion imaging,  axonal flare etc. Axonal flare in response to cinnamaldehyde will be measured using full-field laser perfusion imaging (FLPI) of the target area of skin before and 20 min after sensitization [36] (moorFLPI-2; Moor Instruments). Full field laser perfusion imaging (also known as laser doppler perfusion imaging) quantifies skin perfusion by detecting alterations in reflected laser light resulting from the movement of blood under the skin. Activation of nociceptors in the skin produces a local flare because of release of vasoactive substances which causes an increase in perfusion. This method has previously been used to study the effects of TRPA1 activation by agonists such as cinnamaldehyde [32] and also as a secondary end point in studies of TRPV1 antagonists [37].

#### Cinnamaldehyde application

After baseline QST and skin perfusion imaging the skin will be sensitized by application of trans-cinnamaldehyde (Sigma Aldrich) 10% in ethanol (1 ml) to a 4 × 4 cm area of the participant’s volar forearm for 20 min using a dressing pad covered with an occlusive adhesive dressing. This concentration of cinnamaldehyde (10%) is the lowest concentration known to reliably activate nociceptors and elicit pain and flare. Lower concentrations predominantly evoke itch [38]. The 20 min duration is informed by prior publications measuring thermal thresholds and flare [29, 32, 39]. Participants will then be asked to rate the cinnamaldehyde evoked pain from 0 (no pain) to 10 (worst pain imaginable). They will then be asked to described any evoked sensations. The FLPI and QST will then be repeated.

Study data will be collected and managed using REDCap electronic data capture tools hosted at the University of Bristol [40, 41]. REDCap (Research Electronic Data Capture) is a secure, web-based software platform designed to support data capture for research studies, providing (1) an intuitive interface for validated data capture; (2) audit trails for tracking data manipulation and export procedures; (3) automated export procedures for seamless data downloads to common statistical packages; and (4) procedures for data integration and interoperability with external sources.

### Interim assessment strategy

Interim assessments will be used to determine if the recruitment of the minor allele group should be changed given the likelihood of observing a detectable effect (80% power, ⍺ ≤ 0.05 using independent two tailed t-test) at the end of the study (see Fig. 2). To reduce the impact of performing interim assessments, the criteria for adapting the study are stated a priori and an O’Brien-Fleming alpha spending is used after each hypothesis test [42].

**Fig. 2 Fig2:**
[figure not shown]
Schematic of study design showing the 4 potential outcomes of the adaptive design. The trial progresses from left to right until the full sample of 100 is recruited. Each allele cohort is noted with uniquely coloured human icon with the numbers recruited in that phase noted underneath. Interim assesments are marked with a magnifying glass with the effect size ‘d’ criteria to continue the trial noted and alpha thresholds for subsequent t-test. Note that the trial will adapt due to small effect sizes and also if the hypothesis test passess due efficacy. The final “?” represents that this final cohort could be from any of the final cohorts based on assesment of other outcomes. For further details on the outcome criteria see Table 2

Individuals homozygous for the minor allele(s) and individuals from the control allele group will be recruited until at least 15 members have been recruited to both groups (as determined by simulations see Fig. 3). At this point, an interim analysis will be performed:

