In the event of all minor alleles being underpowered for differences in heat pain threshold, as determined by the interim assessments, additional endpoints derived from the secondary measures (QST and flare) will inform the final group recruitment (see Fig. 3 and Table 2 which illustrate the adaptive design and its effects upon recruitment).

**Table 2 Tab2:** Interim analyses

Interim analysis #	Futility effect size	Efficacy cut-off alpha	Effect size req. for statistical eff (ΔHPT)
1	0.57	0.0013	1.63 (Δ4.1 °C)
2	0.62	0.0023	1.52 (Δ3.8 °C)
3	0.68	0.0055	1.42 (Δ3.5 °C)

Each row indicates the study state at subsequent interims. Effect sizes are displayed as Cohen’s d $$\frac{{\left( {\mu_{minor} - \mu_{major} } \right)}}{\sigma }$$ where µ is the mean and σ is the standard deviation. The futility effect size cut-off is the minimum effect size required to continue the group in the study. The futility effect size is calculated as the smallest effect size observable at the final analysis at 80% probability given an alpha cut-off of 0.05. The efficacy cut-off alpha is the alpha criteria for the interim analysis to determine efficacy. The efficacy cut-off alpha is calculated using an O’Brien-Fleming alpha spending through the gsdesign R package. With subsequent interims the alpha threshold is relaxed as the proportion of information known at interim increases due to the fixed sample size of 15. The effect size required for statistical efficacy (HPT) indicates the minimum effect size (cohen’s d) likely to be observed at 80% power at interim with the corresponding changes in HPT (Δ) indicated assuming σ = 2.5. HPT, heat pain threshold

We will follow the applicable Food and Drug Administration (FDA) guidelines for adaptive trial design [43]. To maintain the integrity of the sampling frame through this experiment, the analysis script is stated a priori and researchers involved in the data collection will not be aware of the outcomes of any interim analysis nor changes in the recruitment strategy; and therefore remain blind to genotype throughout.

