### Data analysis

The hypothesis test at interim and final analysis will be performed using a two-sided independent t-test. The type-1 error is controlled using the O'Brien-Fleming alpha spending method for the primary outcome measure, the heat pain threshold. Other QST variables will only be analysed at the final analysis. All other comparisons between available groups will be treated as exploratory. The genotype of the individuals will also be considered to qualify the association of SNP to any observed effect.

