### Comparison with standard designs

In this study we focused on the heat pain threshold (HPT) of QST as TRPA1 has been implicated in detection of thermal stimuli. The number of participants to recruit for a RbG study is typically calculated from the expected effect size of the variant, however, there is little reliable data upon which to base an effect size calculation for these *TRPA1* SNPs. When an effect size is unknown, an alternative approach is to use estimates of the minimum clinically relevant change. In a reference population, the HPT is 42 ± 2.5 °C (mean ± SD) [44] and we consider a 1.5 °C (*d* = 0.6) change in HPT as being a minimum clinically relevant change (Baron, Maier [45]). In a classic design the number of individuals required for the study can be calculated given a desired probability of observing the effect size at a defined error cut-off. In a standard RbG study design investigating a single minor allele 45 subjects (90 total) would be required in the minor and major allele groups with 80% likelihood of observing an effect at alpha <  = 0.05.

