### Futility

Conversely, there is a chance that the actual mean effect within the sampled population is considerably smaller than the estimated mean effect size. In the classic design this will only be apparent once the full cohort is assessed. Using this adaptive design it is likely that the recruitment of the allele would be stopped at an interim assessment after only 30 participants are recruited. As such, our design reduces the burden on the experimenter and the participants when an effect is unlikely to be observed.

In many studies the sample size is restricted due to practical and financial concerns which can result in the study being of insufficient power to observe clinically relevant changes. In this study we have been resourced to recruit a total cohort of 100 participants where the adaptive design can screen up to 3 cohorts and is powered to detect changes of 1.43 °C (d = 0.57), 1.55 °C (d = 0.62) and 1.7 °C (d = 0.68) at each interim respectively. An analogous, “classical” RbG with multi-armed assessment with 25 participants per group would be powered to detect a difference of 2.03 °C (*d* = 0.81 α <  = 0.05) in the heat pain threshold.

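### Invitation is by genotype alone and the t-test is unadjusted, so chance sex imbalance at 15 v 15 adds a little removable noise if sex affects heat pain threshold

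*Protocol article*

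**What the plan says.** - **Selection.** Participant recruitment describes choosing invitees by their genotype at the five SNPs. No other basis for selection or balancing is named.
- **Interim size.** Interim assessment strategy, for each group: "Individuals homozygous for the minor allele(s) and individuals from the control allele group will be recruited until at least 15 members have been recruited".
- **Test.** Data analysis: "The hypothesis test at interim and final analysis will be performed using a two-sided independent t-test". No covariate is named there or in Interim assessment strategy.
- **Decision rule.** Table 2 lets a minor-allele group continue only if observed d reaches 0.57, 0.62 or 0.68 at the first, second or third interim. The Futility section gives the same values as "1.43 °C (d = 0.57), 1.55 °C (d = 0.62) and 1.7 °C (d = 0.68) at each interim respectively".
- **Protection against confounding.** Background: "Given random allocation of alleles at conception, the RbG design generates study groups in which confounding factors are on average equal".
- **Recruitment mechanism.** A separate group within the ALSPAC recruitment team implements changes in recruitment. The control recruitment rate falls after each switch of allele group, and the same controls serve every comparison.

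**The concern.** Equality on average is a statement about repeated samples. It does not stop one 15 v 15 comparison from having, say, ten women on one side and six on the other. If sex shifts heat pain threshold, that gap moves the observed d, and the plan stops or continues an allele on the observed d. The smallest effect the authors regard as relevant, d = 0.6, lies almost on the cut-off, so small shifts can change individual decisions. Because controls accumulate, an early imbalance among them is carried into later comparisons. What is at stake is precision: some interim noise could be removed at little cost.

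**Working it through.** **Inputs from the article.** Standard deviation: "In a reference population, the HPT is 42 ± 2.5 °C (mean ± SD"). Relevant change: "we consider a 1.5 °C", so d = 1.5/2.5 = 0.6. Significance level in the Table 2 notes: "given an alpha cut-off of 0.05". Interim size 15 v 15; first cut-off 0.57.

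**Assumptions not in the article.** Sex effect s = 0.3, 0.5 or 0.7 SD (0.75, 1.25 or 1.75 °C); proportion female p = 0.5; an allele continues if |d| ≥ 0.57.

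**1. The plan's own figures reproduce.** For d = 0.6, 80% power and two-sided 0.05, the normal formula gives 2 × (1.960 + 0.842)² / 0.6² = 43.6, so 44 per group. The noncentral t gives 45, matching "45 subjects (90 total) would be required in the minor and major allele groups with 80% likelihood of observing an effect". At 50 per group the detectable d is 0.566, matching 0.57.

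**2. How often imbalance occurs.** For two independent Binomial(15, 0.5) counts, P(difference ≥ 4) = 0.200 and P(difference ≥ 5) = 0.099. With p = 0.6 these are 0.191 and 0.092.

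**3. What an imbalance of four does.** Shift in d = (4/15) × s = 0.08 / 0.13 / 0.19. The standard error of d at 15 v 15 is √(2/15) = 0.365, so the middle case is about a third of one standard error. Given such an imbalance, continuation at a true d of 0.6 moves from about 53% to 45% / 39% / 33% if it works against the allele, and to 62% / 68% / 74% if it works in favour.

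**4. Average effect over all draws.** The share of outcome variance due to sex is R² = p(1 − p)s² = 0.0225 / 0.0625 / 0.1225. With sex balanced, the standard error becomes √(2(1 − R²)/15):

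| s (SD) | SE of d | Reduction | Equivalent n per group, 15/(1 − R²) |
|---|---|---|---|
| none removed | 0.365 | – | 15 |
| 0.3 | 0.361 | 1.1% | 15.3 |
| 0.5 | 0.354 | 3.2% | 16.0 |
| 0.7 | 0.342 | 6.3% | 17.1 |

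**5. Effect on decisions.** By the normal approximation, false continuation at d = 0 is 2 × [1 − Φ(0.57/SE)]: 11.9% unbalanced, 11.4% / 10.7% / 9.6% balanced. Simulation with the SD estimated from each sample gives about 13% unbalanced and about 12.5% / 12% / 10.6% after balancing and adjusting. At a true d of 0.6, continuation stays near 54% throughout. The favourable and unfavourable shifts in step 3 cancel, because 0.6 lies so close to 0.57.

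**6. Adjusting without balancing.** Estimating a sex coefficient inflates the variance by roughly 1 + 1/(N − 4), where N is the total in the comparison. At N = 30 the factor is 1 + 1/26 = 1.038, so adjustment alone gains only if R² exceeds 1 − 1/1.038 = 0.037, that is s > √(0.037/0.25) ≈ 0.4 SD. At N = 100 the factor is 1 + 1/96, and break-even falls to about 0.2 SD.

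**The case against.** The strongest reply is that nothing here is an error. The article is silent on sex; how invitations are drawn within a genotype group is operational detail that belongs in a full protocol not shown. A reader might infer that controls are in fact unbalanced on sex, but silence in a condensed article does not establish that. Only the unadjusted t-test is stated outright. That sex affects heat pain threshold is also an assumption, and that sex is on file before invitation is a reasonable inference for a birth cohort but is not stated. All of this stands, and the point is worded conditionally for that reason.

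A reader might also infer that the comparison is biased, since volunteering and telephone exclusions come after conception. The document does not support this. Participants are blind to genotype, and no route is shown by which sex mix would come to differ by genotype. The unadjusted t-test remains valid, because between-sex variance is part of the within-group SD.

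It is also fair that the gain is small. For 0.3 to 0.5 SD it is worth at most about one participant per group, and n = 15 itself is the dominant source of noise. Finally, controls shared across up to three allele groups cannot be exactly re-matched at each interim. That limits the remedy but does not remove it.

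**Conclusion.** The point holds as a minor design improvement. As described, selection by genotype and an unadjusted t-test leave chance sex imbalance in the interim decision. Under assumed sex effects of 0.3 / 0.5 / 0.7 SD and 50% women, removing it cuts the standard error of d by about 1% / 3% / 6% and lowers false continuation from about 13% to 12.5% / 12% / 10.6%. It does not make the interim better at keeping an allele with a true d of 0.6. No figure in the article is wrong on this account. The size rests wholly on a sex effect that the article does not give; if that effect is near zero, so is the gain.

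**What to change.** - **Interim assessment strategy.** Have the independent ALSPAC recruitment group stratify control invitations by sex, so that the sex mix of controls tracks the current minor-allele group as far as the shared control pool allows. Testers' blinding is unaffected, because that group already carries out the recruitment changes.
- **Data analysis, final comparison.** Replace the plain t-test with a linear model in genotype and sex, pre-specified in the a priori script before any interim data are seen.
- **Data analysis, interim.** Include sex only together with the balancing. Define d as the sex-adjusted difference divided by the pooled within-group SD, so that the Table 2 cut-offs keep their scale. Dividing by the residual SD would inflate d: at s = 0.5 SD by 1/√(1 − 0.0625), or about 3%.

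The cost is one degree of freedom, one line in the invitation procedure and a small edit to the script. There are no extra participants or measurements. The downside is a very slight loss of precision if sex has little effect and balance is not achieved. If the full recruitment procedure already balances on sex, only the analysis change remains to be made.
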